### 2.7. Outcomes

The main outcomes of the 24-month cohort-construction phase are:

Number of participants screened, eligible, enrolled, and classifiable by RAI.Frequency of isolated RSWA among enrolled participants.Completeness and quality of vPSG, clinical, neurophysiological, and biosample data.Feasibility of harmonized multicenter eCRF-based data capture.Recruitment rate and retention readiness for long-term follow-up.

The primary long-term clinical outcome is incident RBD, defined by development of clinical dream-enactment behavior with vPSG evidence of RSWA according to accepted diagnostic criteria.

Secondary long-term outcomes include:

Change in RAI over time, when repeat vPSG is available.Development of subthreshold dream-enactment behavior or increased RBD questionnaire scores.Diagnosis of Parkinson disease, dementia with Lewy bodies, multiple system atrophy, or other neurodegenerative disorders.Association between baseline RAI and neurophysiological markers.Association between baseline RAI and blood-based proteomic/metabolomic/glycomic signatures.Attrition, loss to follow-up, and feasibility of repeated annual assessment.

The procedures used to identify and confirm these outcomes during follow-up are described below.

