### 2.8. Follow-up procedures and phenoconversion ascertainment

Participants classified as having isolated RSWA and a comparator group without isolated RSWA will be invited to participate in longitudinal follow-up. Follow-up will be performed at least annually by in-person visit, telephone interview, video consultation, or review of clinical records, according to participant availability and local center procedures. The follow-up strategy is designed to detect two clinically relevant forms of phenoconversion: conversion to clinically manifest RBD and conversion to a neurodegenerative disorder within the alpha-synucleinopathy spectrum, in line with longitudinal evidence from isolated RBD cohorts and biomarker-based models of conversion risk [2,3].

At each follow-up contact, participants will be asked about the occurrence of new dream-enactment behavior, vocalizations or complex motor behaviors during sleep, sleep-related injuries, falls from bed, violent or disruptive sleep behaviors, and changes in sleep quality. Whenever possible, information will also be obtained from a bed partner, caregiver, roommate, or other reliable informant. Follow-up assessments will also record changes in medication exposure, especially antidepressants, benzodiazepines, melatonin, dopaminergic medications, antipsychotics, and other drugs potentially influencing REM sleep muscle tone or parasomnia expression. New diagnoses of sleep disorders, neurological disorders, psychiatric disorders, and relevant systemic illnesses will be recorded.

Incident RBD will be suspected when new recurrent dream-enactment behavior or other clinically relevant REM sleep-related motor behaviors are reported by the participant or an informant. In these cases, participants will be invited to undergo repeat full-night laboratory video-polysomnography, including chin electromyography and video documentation, whenever feasible. Incident RBD will be defined by the emergence of clinical dream-enactment behavior together with polysomnographic evidence of RSWA, according to accepted diagnostic criteria [1,22]. For each suspected or confirmed case, the date of first reported symptoms, date of clinical recognition, and date of polysomnographic confirmation will be recorded separately.

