Phenoconversion to neurodegenerative disease will be assessed through annual clinical history, neurological review, and documentation of any new diagnosis of Parkinson disease, dementia with Lewy bodies, multiple system atrophy, or other relevant neurodegenerative disorders, using established diagnostic frameworks where applicable [23–25]. Follow-up data collection will include symptoms or signs suggestive of parkinsonism, cognitive decline, visual hallucinations, fluctuating cognition, autonomic dysfunction, gait impairment, olfactory impairment, and other non-motor manifestations potentially relevant to prodromal synucleinopathy, consistent with research criteria and updates for prodromal Parkinson disease [26,27]. This approach is also supported by longitudinal application of prodromal Parkinson disease criteria in RBD cohorts [28].

When clinically indicated, participants will be referred for neurological evaluation and additional investigations according to local clinical practice, including neuropsychological testing, autonomic assessment, brain imaging, dopamine transporter imaging, or other biomarker investigations. These tests are not mandated by the protocol but will be recorded when available.

All suspected phenoconversion events will be reviewed by the recruiting center and, when necessary, discussed centrally by the study investigators. Outcome adjudication will use predefined criteria and will distinguish between no conversion, possible RBD, confirmed RBD, possible neurodegenerative phenoconversion, and confirmed neurodegenerative diagnosis. For longitudinal analyses, the event date will be defined as the earliest reliable date of symptom onset when available; otherwise, the date of clinical diagnosis or polysomnographic confirmation will be used. Participants who cannot be contacted will be classified as lost to follow-up after repeated contact attempts, and the date of last available assessment will be recorded.

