### 2.11. Statistical analysis plan

Baseline characteristics will be summarized for the overall cohort and stratified by RSWA status. Continuous variables will be reported as mean and standard deviation or median and interquartile range, according to distribution. Categorical variables will be reported as counts and percentages.

Participants with isolated RSWA will be compared with participants without RSWA. Continuous variables will be analyzed using Student’s t test or Mann-Whitney U test, as appropriate. Categorical variables will be analyzed using chi-square or Fisher’s exact tests. Effect sizes and confidence intervals will be reported whenever possible to avoid overreliance on significance testing.

RAI will be analyzed both as a continuous variable and as a categorical classification variable. Multiple linear regression will evaluate associations between RAI and clinical, pharmacological, sleep, and neurophysiological predictors. Logistic regression will evaluate predictors of isolated RSWA status. Candidate covariates will include age, sex, antidepressant exposure, neurological comorbidity, sleep apnea severity, REM sleep duration, and participating center.

For long-term follow-up, cumulative incidence of RBD will be described using Kaplan-Meier methods. Cox proportional hazards models will estimate the association between baseline isolated RSWA and incident RBD, adjusted for age, sex, medication exposure, center, and relevant sleep-disorder comorbidities. Competing-risk methods may be considered for incident neurodegenerative outcomes or death. Sensitivity analyses will evaluate the influence of antidepressant exposure, minimum REM duration, comorbid sleep apnea, and alternative RAI thresholds.

The extent and pattern of missing data will be reported. If missingness is limited, complete-case analyses will be used. If missingness is substantial and plausibly missing at random, multiple imputation may be considered for regression models. Follow-up attrition will be summarized and compared between RSWA and non-RSWA groups.

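### The event-date rule mixes symptom-onset dates with diagnosis or vPSG dates, so identical courses get different event times and neurodegenerative events can fall before baseline

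*Protocol article*

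**What the plan says.** Section 2.8 sets the date for longitudinal analyses in one sentence: "the event date will be defined as the earliest reliable date of symptom onset when available; otherwise, the date of clinical diagnosis or polysomnographic confirmation". The sentence before it grades events as no conversion, "possible RBD, confirmed RBD, possible neurodegenerative phenoconversion, and confirmed neurodegenerative diagnosis", so the rule applies to both kinds of conversion.

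The outcome definitions are narrower than symptom onset. For RBD: "Incident RBD will be defined by the emergence of clinical dream-enactment behavior together with polysomnographic evidence of RSWA". For neurodegeneration, section 2.7 lists "Diagnosis of Parkinson disease, dementia with Lewy bodies, multiple system atrophy, or other neurodegenerative disorders".

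For each suspected or confirmed RBD case, "the date of first reported symptoms, date of clinical recognition, and date of polysomnographic confirmation will be recorded separately". Follow-up contact is at least annual and may be a visit, a call or a record review. Informants are consulted where possible.

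On analysis, section 2.11 says that "cumulative incidence of RBD will be described using Kaplan-Meier methods", with Cox models for the association between isolated RSWA and RBD. For neurodegenerative outcomes it says only that competing-risk methods may be considered.

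**The concern.** The rule changes the meaning of the time variable from one participant to the next, and the change depends on data availability rather than on disease. Availability is unlikely to be random. Section 2.4 itself warns that having an observer or co-sleeper affects whether dream enactment is recognised, and section 2.8 lets contact mode vary with the participant and the center. An incidence curve built this way is a blend of onset-dated and confirmation-dated events in unknown proportions.

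The rule also has no lower limit at baseline. Section 2.4 excludes people with a prior RBD diagnosis. It excludes neurological disease only when severe enough to prevent valid participation, so someone with early, undiagnosed neurodegenerative symptoms can enroll. If the diagnosis is made during follow-up and the first symptoms predate enrollment, the rule gives a zero or negative event time to an outcome that section 2.7 defines by its diagnosis.

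Section 2.9 says that the longitudinal estimates will be used to plan prevention trials. Early incidence and time to event are what such planning needs.

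**Working it through.** The article gives no onset-to-diagnosis lag, event rate or onset-date availability, so there is no figure of its own to reproduce. The rates and lags below are assumptions chosen to show the size of the effect.

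**1. Same course, two dates.** Dream enactment starts in March, is reported at the annual contact in November, and vPSG confirms it the next April. With a reliable onset date, the event is dated March. Without one, it is dated November or April, 8 or 13 months later. The difference is the full lag.

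**2. Early RBD incidence.** Assumptions: onset hazard 0.06 per year, report at the next annual contact, vPSG 0.1 to 0.9 year (uniform) after the report. The mean lag from onset to confirmation is about 1.0 year. All events without an onset date take the vPSG date. No vPSG date then falls in year 1, so if a fraction *a* of cases has an onset date:

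1-year incidence = *a* × (1 − exp(−0.06)) = *a* × 5.82%

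| *a* | 1-year incidence |
|---|---|
| 100% | 5.8% |
| 80% | 4.7% |
| 50% | 2.9% |
| 0% | 0% |

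Simulation agrees to within 0.1 percentage point. The disease process is the same in every row.

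**3. Five-year RBD incidence.** The definition needs vPSG evidence, so only cases confirmed by year 5 count. Under these assumptions those are the cases with onset by year 4: 1 − exp(−0.24) = 21.3%, whatever the value of *a*.

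**4. Hazard ratio.** Simulated hazards were 0.06 and 0.03 per year (true ratio 2.0), with onset dates available for 90% of cases in one group and 50% in the other, and confirmation by year 5 required. With 90% in the RSWA group the estimate is about 2.03; with the reverse it is about 1.97. Equal availability gives about 2.0. Repeated runs stayed between 1.95 and 2.03.

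**5. Neurodegenerative events dated before baseline.** Assumptions: diagnoses spread evenly over 5 years and an exponential symptom-to-diagnosis lag with mean *m*.

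Share before baseline = *a* × (*m*/5) × (1 − exp(−5/*m*))

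| Mean lag | *a* = 100% | *a* = 80% | *a* = 50% |
|---|---|---|---|
| 1 year | 19.9% | 15.9% | 9.9% |
| 2 years | 36.7% | 29.4% | 18.4% |

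A constant lag *L* gives *aL*/5, which is 20% and 40% at 1 and 2 years with *a* = 100%. The first enrollees (22 February 2024) could be observed for 7.35 years, to 30 June 2031. For them the constant-lag shares fall to 1/7.35 = 14% and 2/7.35 = 27%.

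**The case against.** Using the best available onset date with a fallback is a recognised choice, and the alternatives have weaknesses too. First-report dating depends on when and how people are contacted, and diagnosis dating depends on local referral. For RBD the article asks participants themselves about new behavior at every contact and records a first-symptom date for each case. The fallback may therefore be uncommon, and availability of 50% or 0% is hypothetical. The 0% figure also assumes that nobody is contacted before month 12, whereas contact is at least annual. Baseline dream-enactment history and the requirement for new behavior make RBD onsets before baseline less likely. All of this stands, and it limits the size of the RBD effect. It does not make the rule uniform.

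Three stronger readings are tempting but not supported:

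- **A biased hazard ratio or 5-year incidence.** If onset-dated cases with vPSG after year 5 are counted, the hazard ratio moves to about 2.2 or 1.8, and 5-year incidence ranges from 25.9% down to 21.3%. The RBD definition requires vPSG evidence, and with that imposed both effects nearly vanish.
- **Pre-baseline shares well above 37%.** These need long lags, for instance by treating "olfactory impairment, and other non-motor manifestations potentially relevant to prodromal synucleinopathy" as the onset of the event. The article lists those features for follow-up data collection. It does not say that they date a Parkinson disease, dementia with Lewy bodies or multiple system atrophy event.
- **Neurodegenerative events dropping out of Kaplan-Meier and Cox analyses.** Section 2.11 specifies those methods for RBD only. How non-positive times would be handled could be set out in an analysis plan that is not shown.

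**Conclusion.** The point holds as a defect in a stated rule, not as a missing detail. The rule mixes two time scales and allows neurodegenerative events defined by diagnosis to be dated before baseline.

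The damage is to individual event times and to early cumulative RBD incidence, which could be understated by half if onset dates exist for half of the cases (2.9% against 5.8% at 1 year). The comparison between RSWA groups and the 5-year incidence of confirmed RBD are little affected. For neurodegeneration, roughly 10% to 37% of follow-up diagnoses would get a zero or negative time at mean lags of 1 to 2 years and onset-date availability of 50% to 100%. These sizes rest on the assumed hazard, lags and availability. That the rule produces such times follows from the text alone. It should be changed before longitudinal follow-up starts, but it does not undermine the study's main comparison.

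**What to change.** Use one event-date definition per outcome for all participants.

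- **Neurodegenerative outcomes:** the date of clinical diagnosis.
- **Incident RBD:** a single date type for everyone. This could be the date of first report, or the interval from the last contact without dream enactment to the first contact with it, analysed as interval-censored. Count only cases confirmed by the data cut-off.
- **Sensitivity analysis:** symptom-onset dating, with an explicit rule for onsets before baseline.

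The cost is a change of wording. Section 2.8 already records the three RBD dates separately and documents new diagnoses. Section 2.12 states that longitudinal follow-up has not begun and that the analytical cohort is not yet constituted, so the change can precede any knowledge of outcomes. The downside is that event times become later or less exact for participants who have a good onset date.

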### 2.9. Sample size and recruitment assumptions

DREAMER uses a pragmatic recruitment target based on expected RSWA frequency and feasibility within participating centers. Previous quantitative work in adults without RBD showed that isolated RSWA elevations may be detected in a substantial minority of individuals, with approximately 14% of patients without dream-enactment behavior reaching previously established RBD-level RSWA thresholds [4,7]. Therefore, the initial recruitment target is > 500 participants over 18 months, expected to yield approximately 85 individuals with isolated RSWA. Because the DREAMER population is restricted to adults aged ≥40 years, and because RSWA becomes more frequent with age, the number of isolated RSWA cases may exceed this estimate.

The initial 24-month phase is not designed as a definitive phenoconversion trial. Instead, it is designed to assemble an enriched cohort and collect the standardized baseline data required for adequately powered follow-up. Recruitment assumptions will be reassessed after the first 6 months of enrollment. If the observed frequency of isolated RSWA or the rate of technically classifiable vPSG recordings is lower than expected, recruitment targets may be increased, and the comparator strategy may be adjusted by selecting an age- and sex-matched subgroup without RSWA for long-term follow-up.

Assuming approximately 85 participants with isolated RSWA and long-term follow-up over 5 years, the study may observe a sufficient number of incident RBD events to generate preliminary estimates of relative risk compared with participants without RSWA. These estimates will be used to plan future prevention or neuroprotection trials rather than to support immediate clinical implementation.

### 2.10. Data management and quality assurance

A web-based eCRF will be developed by the coordinating center. The data architecture will include a relational database for storage, a secure web service for data management, and a client-side web application for authorized users. The system will support data entry, display, modification, and controlled deletion according to predefined user permissions.

Data will be pseudonymized before entry into the central database. Access will be role-based and password-protected. The system will be hosted on secure institutional infrastructure. Privacy, cybersecurity, and data-protection procedures will be supervised with involvement of data-protection and information-technology expertise at the coordinating institution.

A data dictionary will define all mandatory, optional, and derived variables. Harmonized fields will include demographic data, vPSG variables, RAI values, sleep-disorder diagnoses, RBD-related symptoms, neurological history, medication exposure, neurophysiological test results, biosample status, and follow-up outcomes.

Quality-control procedures will include:

Standard operating procedures for vPSG acquisition and RAI computation.Training meetings among centers before recruitment.Predefined rules for technical adequacy of chin EMG and REM sleep duration.Automated eCRF range checks and missing-data flags.Periodic cross-center data-quality reports.Central review of ambiguous classification cases.Documentation of protocol deviations.

### 2.11. Statistical analysis plan

Baseline characteristics will be summarized for the overall cohort and stratified by RSWA status. Continuous variables will be reported as mean and standard deviation or median and interquartile range, according to distribution. Categorical variables will be reported as counts and percentages.

Participants with isolated RSWA will be compared with participants without RSWA. Continuous variables will be analyzed using Student’s t test or Mann-Whitney U test, as appropriate. Categorical variables will be analyzed using chi-square or Fisher’s exact tests. Effect sizes and confidence intervals will be reported whenever possible to avoid overreliance on significance testing.

RAI will be analyzed both as a continuous variable and as a categorical classification variable. Multiple linear regression will evaluate associations between RAI and clinical, pharmacological, sleep, and neurophysiological predictors. Logistic regression will evaluate predictors of isolated RSWA status. Candidate covariates will include age, sex, antidepressant exposure, neurological comorbidity, sleep apnea severity, REM sleep duration, and participating center.

For long-term follow-up, cumulative incidence of RBD will be described using Kaplan-Meier methods. Cox proportional hazards models will estimate the association between baseline isolated RSWA and incident RBD, adjusted for age, sex, medication exposure, center, and relevant sleep-disorder comorbidities. Competing-risk methods may be considered for incident neurodegenerative outcomes or death. Sensitivity analyses will evaluate the influence of antidepressant exposure, minimum REM duration, comorbid sleep apnea, and alternative RAI thresholds.

The extent and pattern of missing data will be reported. If missingness is limited, complete-case analyses will be used. If missingness is substantial and plausibly missing at random, multiple imputation may be considered for regression models. Follow-up attrition will be summarized and compared between RSWA and non-RSWA groups.

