## 2. Materials and methods

### 2.1. Objectives

The primary objective of DREAMER is to establish a multicenter, harmonized, trial-ready cohort of adults without clinical RBD in whom isolated RSWA can be identified quantitatively by vPSG and followed longitudinally for the development of RBD.

The secondary objectives are:

To estimate the frequency of isolated RSWA in adults aged ≥40 years undergoing laboratory vPSG across participating sleep centers.To compare clinical, sleep, pharmacological, and neurophysiological characteristics between participants with and without isolated RSWA.To evaluate whether quantitative RSWA severity, measured by the REM Atonia Index (RAI), is associated with clinical and instrumental markers potentially relevant to prodromal synucleinopathy.To create a secure, quality-controlled electronic dataset suitable for future long-term phenoconversion analyses.To establish a biobank and multimodal biomarker framework that can support future mechanistic and prevention-oriented studies.

The long-term objective, beyond the 24-month cohort-construction period, is to determine whether baseline isolated RSWA is associated with higher risk of incident RBD and subsequent neurodegenerative outcomes compared with absence of RSWA.

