**Fig 1 pone.0350467.g001:**
[figure not shown]
DREAMER study workflow. Adults aged ≥40 years undergoing full-night laboratory video-polysomnography are screened for eligibility. After exclusion of participants with prior REM sleep behavior disorder or technically inadequate REM sleep/chin electromyography data, the REM Atonia Index is computed to classify participants with isolated REM sleep without atonia and comparator participants without isolated REM sleep without atonia. Baseline multimodal characterization, secure electronic case report form-based data capture, and longitudinal follow-up support the creation of a trial-ready platform for future prevention studies. RBD, REM sleep behavior disorder; REM, rapid eye movement; EMG, electromyography; RAI, REM Atonia Index; RSWA, REM sleep without atonia; PSG, polysomnography; TMS, transcranial magnetic stimulation; VEMPs, vestibular-evoked myogenic potentials; BAEPs, brainstem auditory evoked potentials; eCRF, electronic case report form.

The study has three operational phases:

**Phase 1: Harmonization and infrastructure development:** During the initial months, participating centers will agree on eligibility criteria, clinical variables, vPSG procedures, RAI computation, ancillary neurophysiological protocols, blood-sample collection procedures, data dictionary, and quality-control rules. A secure web-based eCRF will be implemented.

**Phase 2: Recruitment and baseline phenotyping:** Adults undergoing full-night laboratory vPSG will be screened. Participants without prior RBD and with technically adequate REM sleep recordings will be classified according to quantitative RAI values. Clinical, pharmacological, sleep, neurophysiological, and biobanking data will be collected according to the shared protocol.

**Phase 3: Long-term follow-up:** Participants with isolated RSWA and a comparator group without RSWA will be followed to identify incident RBD and neurodegenerative outcomes. The follow-up component is intended to continue beyond the initial funding period and to provide the evidentiary basis for future risk-stratified prevention trials.

The schedule of screening, baseline, ancillary, and follow-up assessments is shown in Table 2.

**Table 2 pone.0350467.t002:** Schedule of assessments.

Study phase	Procedure	All enrolled participants	Isolated RSWA subgroup
**Screening**	Eligibility review and informed consent	X	X
**Baseline**	Clinical and sleep history	X	X

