### 2.4. Study population, inclusion and exclusion criteria

Participants will be recruited among adults undergoing full-night laboratory vPSG for clinical indications at participating centers. The target population is intentionally pragmatic: it reflects real-world sleep-center populations in which incidental RSWA may be detected and future risk stratification may become clinically relevant.

Participants must meet all of the following criteria:

Age ≥ 40 years at baseline.Ability to understand study procedures and provide written informed consent.Undergoing full-night laboratory vPSG with video recording.Availability of chin electromyographic signal of sufficient technical quality for RAI computation.At least 5 minutes of artifact-free REM sleep.No prior clinical diagnosis of RBD.

Collateral history from a bed partner, roommate, or other reliable informant will be collected whenever available to improve ascertainment of dream-enactment behavior. This is particularly important because the distinction between iRSWA and iRBD may be influenced by the availability of an observer or co-sleeper, potentially leading to under-recognition of dream-enactment behavior [12].

Participants will be excluded if any of the following are present:

Prior diagnosis of RBD.Severe neurological, psychiatric, cognitive, or general medical condition that prevents valid participation or understanding of study procedures.vPSG recordings with major artifacts affecting the chin EMG signal during REM sleep.Less than 5 minutes of artifact-free REM sleep.Withdrawal of consent.

The protocol will record medications known to influence REM sleep muscle tone, particularly antidepressants, as well as comorbid sleep disorders and neurological conditions. These factors will not automatically exclude participation unless specified by the final protocol or judged to preclude valid classification, but they will be incorporated into sensitivity analyses.

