### 2.5. Baseline assessment

At baseline, all participants will undergo standardized clinical assessment, including demographic characteristics, medical history, neurological history, psychiatric history, cognitive status when clinically indicated, sleep history, history of dream-enactment behavior, sleep-related injuries, parasomnia symptoms, and medication exposure. Particular attention will be paid to antidepressants, dopaminergic medications, benzodiazepines, melatonin, antipsychotics, and other drugs that may influence REM sleep physiology or motor behavior during sleep.

Sleep history will include symptoms of insomnia, excessive daytime sleepiness, obstructive sleep apnea, restless legs syndrome, periodic limb movements, narcolepsy-related symptoms when relevant, and other parasomnias. Standardized RBD screening questionnaires may be used as supportive tools but will not replace clinical and vPSG-based classification.

All participants will undergo full-night laboratory vPSG according to the procedures routinely used in participating centers and harmonized through the DREAMER protocol. Recordings will include electroencephalography, electrooculography, submental electromyography, electrocardiography, respiratory channels, limb electromyography, oxygen saturation, body position, and synchronized video. Sleep staging and respiratory and movement events will be scored according to the current standards adopted by each center and harmonized for the variables included in the DREAMER eCRF.

The key classification variable is RSWA quantified by the RAI. The RAI is an automated measure derived from submental EMG amplitude during REM sleep and has been proposed as part of a practical approach to improve diagnostic accuracy and accessibility in RBD assessment [13]. Values range from 0, indicating complete absence of EMG atonia, to 1, indicating stable EMG atonia [14,15]. The DREAMER protocol adopts the established three-level RAI classification: > 0.9 normal, 0.8–0.9 mildly abnormal, and <0.8 definitely abnormal [14–16]. Participants with RAI < 0.85 and no clinical RBD will be classified as having isolated RSWA, while sensitivity analyses will explore alternative RAI thresholds, including <0.8.

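### Undiagnosed dream enactment can remove a participant from the isolated RSWA group but not from its comparator, which tilts the baseline group contrast and logistic model against RSWA for variables tied to dream enactment

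*Protocol article*

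**What the plan says.** All places are in the protocol article.

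- **Index group (2.5).** "Participants with RAI < 0.85 and no clinical RBD will be classified as having isolated RSWA". Two conditions apply, one on RAI and one on clinical RBD.
- **Comparator.** Section 2.11: "Participants with isolated RSWA will be compared with participants without RSWA". Phase 3 in 2.2 and the ancillary tests in 2.6 also use absence of RSWA. The Fig 1 legend has "comparator participants without isolated REM sleep without atonia", and 2.8 likewise refers to absence of isolated RSWA. No version sets a condition on dream enactment.
- **Entry (2.4).** "No prior clinical diagnosis of RBD". This applies at any RAI. Dream enactment without a diagnosis is not an exclusion.
- **What counts as RBD (2.7 and 2.8).** For incident cases: "Incident RBD will be defined by the emergence of clinical dream-enactment behavior together with polysomnographic evidence of RSWA".
- **Analyses (2.11).** Besides the group tests there is a logistic model of isolated RSWA status, and "Multiple linear regression will evaluate associations between RAI and clinical, pharmacological, sleep, and neurophysiological predictors". The candidate covariates are age, sex, antidepressants, neurological comorbidity, apnea severity, REM duration and center. The sensitivity analyses cover antidepressants, REM duration, apnea and RAI thresholds. Dream enactment is in neither list.
- **Objective served (2.1).** "To compare clinical, sleep, pharmacological, and neurophysiological characteristics between participants with and without isolated RSWA".
- **Data held.** Section 2.5 records dream-enactment history, injuries and parasomnia symptoms in everyone. Table 2 lists an RBD symptom or questionnaire assessment for everyone. Section 2.4 adds informant history where available.

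**The concern.** The two groups are meant to differ by RAI, but the definitions also make them differ by how dream enactment is handled. With low RAI, recognised clinical dream enactment makes RBD and ends membership of the index group. With high RAI, the same history generally does not make RBD, because RBD needs RSWA, so the participant stays as a comparator.

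Part of any baseline difference in dream enactment, and in whatever travels with it, is then produced by the group definition. Objective 2 compares clinical characteristics between these groups, and features tied to dream enactment are among the most relevant to a prodromal reading. A true excess in isolated RSWA could be diluted, hidden or, for dream enactment itself, reversed. The concern is with the baseline analyses and not with the Cox model for incident RBD.

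**Working it through.** **1. Inputs.** From 2.9: more than 500 recruited and about 85 with isolated RSWA. The article states no bias, power or effect-size figure for the baseline contrast, so there is nothing of that kind to reproduce. The 85 serves here only for group size. It is 17% of 500; the cited 14% would give 500 × 0.14 = 70, or would need 85/0.14 ≈ 607 recruits, a separate matter. The other group is taken as 500 − 85 = 415.

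Assumed, because not given: dream-enactment prevalence d (5 to 30%), the share of low-RAI enactors labelled RBD (80 or 100%), the marker shift δ with dream enactment (0.2 to 0.8 SD), and two-sided alpha 0.05.

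**2. Dream enactment itself.** Take d = 10% at every RAI, so the true odds ratio is 1. Of 100 low-RAI participants, 10 enact dreams and 8 are labelled RBD and leave. That leaves 2 of 92 = 2.2%, against 10% in the comparator.
- Odds ratio = (2/90)/(10/90) = 0.2, which is 1 minus the labelled share.
- If the truth is 10% with low RAI and 5% with high RAI, the true odds ratio is (10/90)/(5/95) = 2.1. Observed: 2.2% versus 5.0%, odds ratio (2/90)/(5/95) = 0.42. The direction reverses.
- Full labelling gives 0% versus 10% and removes 500 × 0.17 × 0.10 = 8.5 participants. This is the extreme case.

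**3. Indirect binary marker.** Present in 30% of enactors and 10% of others, d = 10%, 80% labelled, no true association with RAI.
- Index: 0.0217 × 0.30 + 0.9783 × 0.10 = 0.104. Comparator: 0.10 × 0.30 + 0.90 × 0.10 = 0.120.
- Odds ratio = (0.10435/0.89565)/(0.120/0.880) = 0.85, truth 1. Over d = 5 to 15% and 80 to 100% labelled, it runs from 0.92 down to 0.74.

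**4. Indirect continuous marker.** With full labelling, bias relative to a symmetric rule = −d × δ. The standard error with 85 versus 415 is √(1/85 + 1/415) = 0.119 SD. Power is for a true difference of 0.35 SD; under a symmetric rule it is 84%.

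| d | δ (SD) | Bias (SD) | Power | Rejection rate if no true difference |
|---|---|---|---|---|
| 5% | 0.2 | −0.010 | 81% | 5.1% |
| 10% | 0.5 | −0.050 | 71% | 7.0% |
| 10% | 0.8 | −0.080 | 62% | 10.3% |
| 20% | 0.5 | −0.10 | 56% | 13.4% |
| 30% | 0.8 | −0.24 | 15% | 52.2% |

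With 80% labelled, the second row becomes −0.5 × (0.10 − 0.0217) = −0.039 SD. If δ = 0 the bias is zero; if δ is negative its sign flips.

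**5. Comparator wording.** In a simulation (1,000,000 draws, d = 10%, δ = 0.5, 17% low RAI, dream enactment independent of RAI), a true difference of 0.18 SD appears as 0.13. It appears as 0.115 if newly recognised RBD is counted as comparator, which absence of isolated RSWA literally allows.

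**6. Linear RAI regression.** Same simulation.
- All classifiable participants kept: dream enactment has no association with RAI, as it should.
- Low-RAI enactors dropped: a spurious association of +0.31 SD with higher RAI, and the marker slope on RAI moves from −0.099 to −0.087.
- With dream enactment truly related to low RAI (latent correlation 0.3), the marker slope is −0.125 with nobody removed, −0.101 after the one-sided removal and −0.099 after excluding enactors on both sides. Restricting both groups therefore does not recover the full-sample slope; keeping everyone does.

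**The case against.** A reader might infer that the isolated RSWA group is emptied of dream enactment, that nobody with RAI of 0.85 or more can have RBD, and that every RAI analysis will make low RAI look benign. The documents do not support this.

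- Section 2.5 requires absence of clinical RBD, not of all dream enactment. Section 2.7 treats subthreshold dream enactment as a separate state, and the Discussion allows that isolated RSWA may include subclinical RBD. The 0% figure is a bound.
- The 0.85 cut-off defines isolated RSWA. It is not stated as the RSWA criterion for RBD, and 2.5 grades 0.8 to 0.9 as mildly abnormal. Selection therefore falls mainly, not exclusively, on the low-RAI side.
- A prior RBD diagnosis is excluded at any RAI, so the asymmetry comes from cases first recognised at baseline.
- Section 2.11 does not say that newly recognised RBD leaves the linear regression. The description of the cohort in 2.1 as adults without clinical RBD makes that plausible, but does not establish it.
- Dream-enactment frequency is not given, and at 5 to 10% the bias in indirect markers is below 0.1 SD.
- Requiring no dream enactment in both groups changes the population described and removes subthreshold enactors from the index group.
- Some detail may lie in documents not shown; 2.12 mentions a prespecified matching strategy.

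These points narrow the reach and temper the size. They leave the core intact: 2.11 names its contrast, covariates and sensitivity analyses, and none handles dream enactment. The only matching factors that the article names, in 2.9, are age and sex.

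**Conclusion.** The concern holds for the baseline group contrast and for the logistic model of isolated RSWA status. For dream-enactment history, sleep injury and RBD questionnaire scores, the comparison is partly settled by the definitions. For markers that rise with dream enactment, the bias runs against RSWA; inversely related markers shift the other way. The linear RAI regression is a conditional problem: it arises only if newly recognised low-RAI RBD is dropped.

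The size cannot be fixed from the documents. On the assumptions shown, it is large for dream enactment itself (odds ratio about 0.2 when the truth is 1). For indirect markers at 5 to 10% prevalence it is small: 0.01 to 0.05 SD for shifts of 0.2 to 0.5 SD, and 0.08 SD for a shift of 0.8 SD at 10%. It becomes material at 20 to 30%. This should be corrected, and it is cheap to correct now, since 2.12 says the analytical cohort has not yet been constituted.

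**What to change.** In 2.11, with matching wording in the Fig 1 legend, 2.6 and 2.8:

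1. Use one comparator definition throughout: without RSWA, and not including RBD newly recognised at baseline. State how clinical RBD is judged at baseline and where newly recognised cases are placed.
2. Alongside the contrast by the 2.5 definition, run the RSWA contrast and the logistic model with the same dream-enactment rule in both groups, using the participant and informant history already collected. Draw ancillary-test comparators from the same pool.
3. Report dream enactors with RAI of 0.85 or more as a separate descriptive group.
4. State that group differences in dream enactment, sleep injury or RBD questionnaire scores will not be interpreted as findings.
5. Fit the linear RAI regression in all classifiable participants, including newly recognised RBD, at least as a sensitivity analysis.

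**Cost.** Wording and a few extra model fits; no new data. At 5 to 15% prevalence the symmetric contrast loses about 21 to 62 of 415 comparators (415 × 0.05 to 415 × 0.15) and some subthreshold enactors from the index group. It then describes adults without dream enactment, which is why it belongs beside the 2.5 contrast and should not replace it. Because informant history is not always available, some dream enactment will be missed in both groups.
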